## Abstract

Previous studies of multiple languages have found processing differences between patient-first and agent-first word orders. However, the results are inconsistent as they do not identify a specific ERP component as a unique correlate of thematic role processing. Furthermore, these studies generally confound word order with frequency, as patient-first structures tend to be infrequent in the languages that have been investigated. There is evidence that frequency at the sentence level plays a significant role in language processing. To address this potential confounding variable, we will test a language where the non-canonical sentences are more frequent and are comparable to the canonical sentences, namely Standard Indonesian. In this language, there is evidence from acquisition, corpus, and clinical data indicates that the use of passive is frequent and salient. One instance of this difference can be demonstrated by the fact that it has been suggested that frequency may be the reason why Indonesian-speaking aphasic speakers do not have impairments in the comprehension of passives, whereas speakers of other languages with aphasia often do. In the present study, we will test 50 native speakers of Indonesian using 100 sentences (50 active and 50 passive sentences). If the neural correlates of thematic role processing are not observed in the critical region of the sentence (the prefix of the verb), this would suggest that the previous results were indeed influenced by frequency, but if we find that specific ERPs are connected to the hypothesized syntactic operations, this would further reinforce the existing evidence of the increased cognitive load required to process more syntactically complicated sentences.

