## Method

### Participants

50 right-handed, healthy, native speakers of Indonesian will participate, and be tested at the Hong Kong Polytechnic University. All the participants will be tested using an Indonesian translation of the short form of the Edinburgh Handedness Inventory [34] to ensure that they are classified as right-handed. Participants will provide informed consent and will be financially compensated. As a power analysis is not possible due to the lack of previously studies on non-anomalous sentence processing, we will use a heuristic estimate of the sample size needed by doubling the largest sample size of previous relevant studies we found on non-anomalous sentence processing: Jackson, Lorimor, & van Hell [15] had 25 participants, and therefore the proposed study will recruit 50 participants. We will recruit participants from both within the university (students and/or staff) as well as outside of it. The participants will have to complete a language background questionnaire to ensure that they have first-language or equivalent proficiency in Indonesian. This study was approved by the Hong Kong Polytechnic University’s Institutional Review Board (ref no. HSEARS20211223003). Written consent will be obtained from participants.

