### Statistical analysis plan

The statistical analysis will be conducted using cluster-based permutation tests [45] over all the scalp electrodes and the entire post-stimulus epoch. The advantage of this approach is that it allows testing for effects anywhere on the scalp and any time in the epoch, while still controlling the familywise false positive rate, and without the experimenter needing to choose regions and time windows for analysis. The test works by comparing the active and passive ERPs at each channel and each sample and identifying clusters of spatiotemporally adjacent data points where the difference between the two conditions exceeds some threshold; in our analysis, that threshold will be two-tailed p < .1 in a t-test. In other words, a t-test comparing active and passive will be performed at every sample in every channel, if a series of several time points in a row on the same channel and/or several adjacent channels at the same time all exceed this threshold, they are treated as a "cluster". Next, each cluster is assigned a test statistic (in our case, the test statistic for a cluster is derived by summing the *t*-values of all the samples in the cluster), and the largest cluster-level test statistic in the epoch is taken as the observed test statistic for the data. Next, the data are randomly permuted (i.e., within each subject, the condition labels "active" and "passive" may be randomly switched) several thousand times, and with each random permutation the abovementioned procedure of identifying clusters and calculating a test statistic is repeated. This yields a permutation distribution of several thousand test statistics, against which the original observed test statistic is compared. The proportion of permutation test statistics that are larger than the original observed test statistic is the *p*-value for the test; if there is a significant difference between the active and passive ERPs then this value will be small. See [45] for a more detailed explanation of how this test works.

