## Predictions

There are several possible patterns of the results. These are described below.

An ERP contrast can be expected between canonical and non-canonical sentences on the critical region (verb). We can expect a posterior positivity (P600) at the disambiguation point to indicate that a revision of the thematic information is needed: NP1 should be reassigned from the default agent role to become the patient of the action.An ERP contrast can be expected between canonical and non-canonical sentences in the NP2 time windows. Additionally, based on earlier studies we expect a ‘generalized’ increase in processing costs in comprehending the non-canonical structures attributed to violation of transitivity expectation [16] as well as retrieval of verbal material in a non-canonical position and uptick in working memory demands [19]. For example, the verbs in Basque [19] and Japanese [16] provide no additional thematic information, but within that section, ERP differences for object-first compared to subject-first structures were observed.A lack of ERP correlates in both the verb and NP2, especially between the passive and active conditions, suggests that previous findings regarding the neural correlates of thematic role assignment were confounded by syntactic frequency because the studies compared one highly frequent structure (e.g. active) to a highly infrequent sentence structure (e.g. passive).

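### A non-significant difference test is to be read as support for the frequency account, with no criterion for the null and no detectable effect stated

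*Protocol article*

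**What the plan says.** The Predictions section lists three possible result patterns. The third gives a null result a substantive meaning: finding no ERP difference at either the verb or NP2 "suggests that previous findings regarding the neural correlates of thematic role assignment were confounded by syntactic frequency". This rule needs a null in two epochs, verb and NP2. The Abstract looks only at the verb prefix and says of a null there that "this would suggest that the previous results were indeed influenced by frequency".

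The inferential method is in the Statistical analysis plan section: "cluster-based permutation tests [45] over all the scalp electrodes and the entire post-stimulus epoch". It compares active with passive, forms clusters at a two-tailed threshold of p < .1 and uses 5000 permutations. The threshold was chosen for sensitivity to weak, sustained effects. It is not the significance level of the test, and no numerical level for the cluster p-value is given.

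On sample size, the Participants section states: "As a power analysis is not possible due to the lack of previously studies on non-anomalous sentence processing". It then sets the number by "doubling the largest sample size of previous relevant studies we found on non-anomalous sentence processing"; that study "had 25 participants", so 50 will be recruited. Predictions gives the expected direction and window (verb 500-700 ms, passive more positive; NP2 300-600 ms, passive more negative) but no amplitude.

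**The concern.** A non-significant test of a difference means that no difference was detected. It does not separate a negligible effect from one that was missed. To argue from a null to an explanation of earlier findings, the plan must say how small an effect has to be before it counts as none, and must be able to show that the data exclude anything larger. The article does neither, and an inconclusive outcome is not among its listed patterns.

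This matters because the Frequency section makes control of frequency the main aim, so the null branch is one of the two conclusions the study is built to reach. A real but modest effect that goes undetected would be reported as support for the frequency account.

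The reason given for having no power analysis does not cover a sensitivity calculation. That needs only the sample size, a significance level and a target power, and no earlier effect estimate.

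**Working it through.** **Inputs from the article.** N = 50, each participant reading both conditions (Participants, Materials). Largest earlier sample 25 (Participants). Null rules as described above (Abstract, Predictions).

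**Assumptions, not in the article.** Two-sided level 0.05; dz values of 0.2 to 0.5; 40 retained after exclusions. The Data exclusion criteria section lists several exclusion rules but no expected rate. The proxy is a paired t-test on one prespecified mean amplitude, because cluster-test power depends on the extent of the effect and on noise that the article does not give.

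**1. The plan's own figure.** 2 × 25 = 50. It reproduces, but it is a heuristic and carries no power statement.

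**2. Detectable effect.** Normal approximation: dz = (1.960 + 0.842)/√50 = 2.802/7.071 = 0.396. With the noncentral t distribution:

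| Retained n | dz for 80% power | dz for 90% power |
|---|---|---|
| 50 | 0.40 | 0.47 |
| 40 | 0.45 | 0.53 |

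**3. Chance of missing a real effect.** Power = P(T > t_crit), where T is noncentral t with n − 1 degrees of freedom and noncentrality dz√n. For dz = 0.3 and n = 50 the noncentrality is 0.3 × 7.071 = 2.12, t_crit = 2.01 and power = 0.548, so the miss rate is 1 − 0.548 = 0.452.

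The joint column applies when the same dz is present in both epochs and the two tests are independent; it is the single miss rate squared.

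| dz | n | Power, one test | Missed, one test | Missed in both epochs |
|---|---|---|---|---|
| 0.2 | 50 | 28% | 72% | 51% |
| 0.3 | 50 | 55% | 45% | 20% (0.452²) |
| 0.4 | 50 | 79% | 21% | 4% |
| 0.2 | 40 | 23% | 77% | 59% |
| 0.3 | 40 | 46% | 54% | 30% (0.544²) |
| 0.4 | 40 | 69% | 31% | 9% |

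The single-test column fits the Abstract's verb-only rule, or an effect that exists in one epoch only. The joint column fits the Predictions rule. As the two tests become positively correlated, the joint rate rises towards the single-test rate.

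**4. What 50 participants could support as an equivalence claim.** Two one-sided tests at 0.05 each, true difference zero: 80% power needs a bound of about dz 0.42 at n = 50 and 0.47 at n = 40. If both epochs must pass and are independent, 80% per epoch becomes 0.80² = 64%. A bound of dz 0.3 would need 97 participants for 80% power in one epoch.

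**5. Why a bound cannot be chosen by what 50 participants afford.** At n = 50, a true dz of 0.3 would be declared equivalent about 17% of the time with a bound of 0.40 and about 27% with a bound of 0.45. If 0.3 matters scientifically, those bounds are too wide. The article does not say whether it does.

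**The case against.** The strongest defence has four parts.

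*The wording is hedged.* Both places use the language of suggestion. This stands and lowers the severity. It is still a prespecified positive reading of non-significance.

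*The sample is twice the largest relevant earlier one, and the inference concerns effects already reported.* If the closest study (25 participants) had used one paired two-sided 0.05 test, the smallest significant dz would be 2.064/√25 = 0.41. At 50 participants, power for a true dz of 0.41 is about 81%. The article does not state that study's test, and published effects can be inflated, so this does not establish adequacy. It does show that sensitivity is reasonable for effects of that size, and that dz 0.2 to 0.3 is the unfavourable end of the range.

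*Quality rules guard against noisy nulls.* The minimum of 25 trials per condition and the 3.0 dB signal-to-noise limit make a null due to noise less likely. They are not evidence that an effect is absent.

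*A windowed equivalence test answers a narrower question than the whole-epoch test.* This is right. Equivalence in one window and region cannot show that no ERP difference exists anywhere, so any conclusion must be limited accordingly.

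A reader might also infer that a dz of 0.3 would yield the frequency conclusion about half the time under the plan generally, and more often still with the whole-epoch cluster test. The article supports neither. The 45-54% figure does not apply to the Predictions rule when the effect is in both epochs and the tests are independent. Whether the cluster test has more or less power than the proxy cannot be settled without the effect's extent and the noise.

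**Conclusion.** The point holds as a flaw in the planned inference. The article ties a substantive conclusion to non-significance, and the planned analysis offers no way to tell an absent effect from a missed one. On the proxy, effects below about dz 0.40 (0.45 with 40 retained) are detected with less than 80% power. A dz of 0.3 is missed 45% (54%) of the time under the verb-only rule, and about 20% (30%) under the two-epoch rule if the effect is in both epochs and the tests are independent.

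These figures rest on an assumed two-sided level of 0.05, an assumed retention of 40, and a single-contrast t-test in place of the cluster test. They do not show that 50 is too few: the smallest effect that matters is not stated, so adequacy can only be shown as a range. The test for a difference itself is not in question. Severity: should be fixed.

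**What to change.** 1. **Null rule.** State that a non-significant result in both epochs is inconclusive on the frequency account unless a prespecified criterion for the null is met. One workable form is an equivalence test or Bayes factor on the passive-minus-active mean amplitude in the windows already predicted (verb 500-700 ms, NP2 300-600 ms), over a named electrode region. Justify the bound by a smallest effect of interest, not by the sample size. Require the criterion in both epochs, limit the conclusion to those windows and that region, and report the estimates with confidence intervals.
2. **Sensitivity.** Replace the statement that power cannot be analysed with the detectable effect at 50 and at plausible retained numbers, at a stated significance level.
3. **Consistency.** Reconcile the Abstract's verb-only rule with the verb-and-NP2 rule in Predictions.

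The cost is some wording and one added analysis. The downside is that some null results will have to be called inconclusive, and 50 participants support only a fairly wide bound (about dz 0.42 for 80% power per epoch). If the justified bound is tighter, the choice is between more participants and accepting that a null may not be interpretable.

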## Results

### Timeline

Funding and research staff have already been secured for this project. With the assumption that this *Registered Report Protocol* is accepted, we hope to carry out data collection during fall 2022-or as soon as we receive an in-principle acceptance notice, complete the data analysis within winter 2022 (as most of the data processing steps described in the manuscript are automated, this step can be completed very quickly), and we will submit the *Registered Report* by spring 2023. One potential issue here is that our institution is in a location where Indonesian is not the first language for most of the population. However, we believe we will still be able to recruit a sufficient number of participants from the immigrant and student population.
